
### Data management

All consent forms will be stored in a master file, which will be kept in a locked drawer where only members of the research team have access. All case report forms will not be linked to names, just a participant number, and kept in a separate locked cabinet where only the research team has access. All data, including video and audio recordings, will be held on an encrypted hard drive only members of the research team can access. Data will be stored for 5 years after the study and will then be deleted or destroyed.

### Analysis

All data will be entered into a database by an RA and verified by the second RA using double data entry to ensure data quality. As this is a feasibility study, we will examine missing data as an outcome.

Descriptive statistics will be summarised to understand the demographic variables relating to the recruited population. Descriptive statistics and plots will be used to assess the distribution of the measurement tools, repeated at baseline and follow-up and by each arm. We will also examine the distributions of scores in the different language groups to see to what extent item scores and overall distributions differ or are similar. Correlations between our two measurement tools will be calculated.

To determine if the intervention is deliverable, we will record the number of sessions that the Kanyeleng groups delivered, aiming to deliver two thirds of the sessions, and the duration of each session, aiming to last between 45 and 75 min. We will also perform a qualitative evaluation, using the video and audio recordings, to determine intervention fidelity at the four sites. Both RAs will watch the video and audio recordings of the first and fourth group-singing sessions at each clinic and complete a checklist to determine if all the necessary elements—as outlined in the training workshops—were included in the intervention. Reliability of the fidelity measure will be ascertained by measuring inter-rater consistency.

We will also calculate the proportion of clinics approached that consented, aiming to reach over 50% recruitment rate, and record any scheduling problems in keeping with the stepped wedge timeline. Recruitment, adherence and completeness of data will be calculated for both groups. We aim to achieve a 60% recruitment rate and no more than 30% attrition in both arms. To determine if the intervention was culturally appropriate and well received by the community and health workers, we will collect qualitative data from post-intervention interviews and perform a thematic analysis.

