### Objectives

Our primary objective is to test (a) the feasibility of delivering a group-singing intervention to a sample of pregnant women in The Gambia using a stepped wedge design and (b) the feasibility of using standardised tools to measure the impact of this intervention on anxiety and depression symptoms, before and after the intervention.

This objective can be broken down into five specific feasibility objectives:
To obtain demographic information on the eligible populationTo determine if our measurement tools, the Edinburgh Postnatal Depression Scale (EPDS) and the Self-Reporting Questionnaire (SRQ-20), are useableTo determine if the intervention is deliverableTo determine if the stepped wedge trial design is deliverable and obtain information that will inform the definitive study. Specifically to:
Assess recruitment and acceptability of randomising clinicsAssess the recruitment rate of women to control and intervention groupsAssess participants’ adherence to the intervention group and follow-up in both armsTest the feasibility of data collectionTo determine if this type of intervention is culturally appropriate and well received by the community and health workers.

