### Intervention

The intervention will be delivered on the community level, meaning that it will include women with a range of anxiety and depression symptoms. Our primary aim is to reduce symptoms in those experiencing them (whether these are at a high level or a medium or low level). We anticipate this may also help to reduce their symptoms into the postnatal period. By including those with low and high levels of symptoms, rather than screening and including only those with high levels of symptoms, we will aim to avoid stigma and increase acceptability.

The intervention has been developed following focus groups with various stakeholders including health professionals (midwives and community birth companions), pregnant women and musicians (griots and Kanyeleng groups).

Four groups of 20 women between 14 and 24 weeks gestation will attend six 60-min group-singing sessions at their local antenatal clinic. This will take place in the morning as this is the time deemed to best suit the majority of women and clinics. Local Kanyeleng groups who specialise in musical practices to support women’s health will lead the sessions. The content of the six sessions will be co-designed with the Kanyeleng groups via two extended workshops with the research team. All sessions will begin with a welcome song and end with a closing song. Some of the songs used during the main body of the session will cover topics including the (a) importance of the singing group in supporting each other, (b) importance of other positive relationships in their lives, (c) resilience to challenges and empowerment and (d) importance of being open, removing stigma to discuss challenges. One lullaby will be introduced at each session. Kanyeleng leaders will also be encouraged to ensure that all the women feel comfortable and are participating when they can.

The nature of the intervention will necessarily vary somewhat across the four settings, especially as Wolof speaking groups and Mandinka groups have different and distinct cultural beliefs, practices and language. By using the Kanyeleng groups local to each of the four clinics involved, the sessions will be contextually appropriate, while the workshop with all four Kanyeleng groups before the intervention begins will ensure that the overarching goals, content and approach to session delivery are broadly standardised.

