### Sample size

As this is a feasibility study, it is not designed to assess the efficacy of the intervention, although pilot data on this will be collected. We will evaluate the feasibility of study design, data collection and whether the intervention is deliverable and acceptable to the participants. In the study, we will gather information to be used in the design of the future definitive study including an estimate of the standard deviation of potential primary outcomes to inform the sample size. We aim to collect data from a total of 120 pregnant women, 60 in the control condition and 60 in the intervention condition [27]. This number will be sufficient to provide estimates of binary feasibility outcomes with precision of at least ± 9 percentage points for the 95% confidence interval.

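### The planned EPDS and SRQ-20 summaries are all cross-sectional, so they do not yield the within-woman change or the baseline-to-later correlation needed to size the definitive trial

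*Protocol article*

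**What the plan says.** The Analysis section of the protocol article sets out three summaries of the EPDS and SRQ-20. The first is by arm and time point: "Descriptive statistics and plots will be used to assess the distribution of the measurement tools, repeated at baseline and follow-up and by each arm". The second compares item and total score distributions between language groups. The third is the correlation between the two scales. Each describes scores at one occasion.

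Three other places bear on this:

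- Objectives, part (b) of the primary objective, is the feasibility of using standardised tools "to measure the impact of this intervention on anxiety and depression symptoms, before and after the intervention".
- Sample size says the study will supply "an estimate of the standard deviation of potential primary outcomes to inform the sample size". It does not say whether this is the SD of the raw score, of change, or of the later score adjusted for baseline.
- Incentive and participant retention, and Trial schedule, have every woman assessed at baseline (week 1), post (week 7) and follow-up (week 11).

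**The concern.** The design collects repeated measures on the same women, but the stated analysis does not use the pairing. Distributions at two separate times do not determine how individual women moved between them. If one woman goes from 15 to 5 and another from 5 to 15, the two distributions are the same as if neither had changed.

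Two quantities are lost: the spread of within-woman change and the correlation between baseline and later score. Both bear on whether the scales can register change in individuals, which is part of what objective (b) asks. Both are also planning inputs. A definitive trial with a baseline measure would usually adjust for it, and the sample size then depends on the baseline-adjusted SD. If only the raw SD is passed on, the correlation must be guessed or the adjustment ignored.

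**Working it through.** **The plan's own figure.** The only numerical basis for the sample size is "precision of at least ± 9 percentage points for the 95% confidence interval". With n = 120 and p = 0.5, the half-width is 1.96 × √(0.25/120) = 0.0895, or 8.95 points, so the figure reproduces. It concerns binary feasibility outcomes and has no bearing on the scale scores. The document gives no SD, correlation, effect size or power for the EPDS or SRQ-20, so what follows is a range under assumptions.

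**Inputs.** Raw SD set to 1 and taken as equal at baseline and at the later time (assumption). Baseline-to-later correlation ρ = 0.3, 0.5 or 0.7 (assumption). Women per arm: 60 (Sample size), or 60 × 0.7 = 42 at the 30% attrition limit (Analysis).

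**Formulas.** For a fixed difference in means, error rate and power, the sample size is proportional to the variance of the analysed score.

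- Raw later score: variance 1.
- Change score: variance 2(1 − ρ).
- Later score given baseline: variance 1 − ρ².

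**Results.**

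| ρ | SD of change | N relative to raw | Baseline-adjusted SD | N relative to raw |
|---|---|---|---|---|
| 0.3 | √1.40 = 1.18 | 1.40 | √0.91 = 0.95 | 0.91 |
| 0.5 | √1.00 = 1.00 | 1.00 | √0.75 = 0.87 | 0.75 |
| 0.7 | √0.60 = 0.77 | 0.60 | √0.51 = 0.71 | 0.51 |

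The marginal distributions are the same in all three rows. The planned summaries therefore cannot say which row applies. Sizing a baseline-adjusted analysis from the raw SD would overstate N by a factor of 1/0.91 = 1.10 at ρ = 0.3, and 1/0.51 = 1.96 at ρ = 0.7. Sizing a change-score analysis from it would understate N at ρ = 0.3, where 1.40 times as many women are needed.

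**Can this study estimate these quantities?** The 95% interval for an SD runs from 0.85 to 1.22 times the estimate with 60 women, and from 0.82 to 1.28 with 42. For a correlation of 0.5 in 42 women, Fisher's transformation gives 0.549 ± 1.96/√39 = 0.235 to 0.863, which is 0.23 to 0.70 on the correlation scale. These intervals ignore clustering by clinic. The estimates would be rough but better than a guess, and should be reported with their intervals.

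**The case against.** **This is a feasibility study.** Sample size says "it is not designed to assess the efficacy of the intervention, although pilot data on this will be collected", and descriptive distributions suit the objective of finding out whether the scales are usable. That stands against any demand for an efficacy analysis. It does not touch the present point, which asks for no test and concerns a planning quantity that the same section promises.

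**Mean change is already visible.** Among women measured at both times, mean change equals the difference between the two means, so the group-level change and its contrast with control can be read from the planned summaries. This stands. What is lost is the spread of change and the correlation.

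**The SD may be defined elsewhere.** The article does not tie the SD to the raw whole-arm score, and a full protocol or analysis plan could define it. This also stands: the text does not show that a wrong SD will be used. It shows that its type is left open while the stated summaries are all cross-sectional. Records are kept by participant number, so the paired figures can be produced without any change to the design.

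**Stronger readings a reader might infer.** One is that the analysis fails the study's primary aim, because the Intervention section says "Our primary aim is to reduce symptoms in those experiencing them (whether these are at a high level or a medium or low level". That sentence describes what the singing sessions are for. The study's primary objective is feasibility.

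Another is that averaging over unscreened women dilutes the effect so much that the definitive trial would need 6 to 25 times as many women. That takes 20% to 40% as the share able to benefit (1/0.4² = 6.25; 1/0.2² = 25) and assumes no effect in anyone else. The same sentence counts low-level symptoms, so the target group may be nearly everyone. At 90% the factor is 1/0.9² = 1.23. The documents do not support the larger figures.

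**Conclusion.** The point holds as a modest improvement to the score analysis. The Analysis section uses none of the pairing in the data, and so leaves out the spread of within-woman change and the baseline-to-later correlation. At correlations of 0.3 to 0.7, the definitive sample size would be 0.91 to 0.51 of the raw-SD figure with baseline adjustment, and 1.40 to 0.60 of it with change scores.

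These factors rest on assumed correlations, equal SDs at the two times, and a comparison of individual means without clustering; none of these comes from the document. The conclusion does not extend to saying that the study misses its objective, that its summaries cannot show change in group means, or that an unsuitable SD will certainly be used.

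**What to change.** In **Analysis**, add for each scale and arm, at week 7 and week 11:

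- change from baseline in women measured at both times, with a 95% confidence interval for the mean and its SD;
- the correlation between baseline and later score, with its interval;
- the SD of the later score given baseline.

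Naming both weeks also removes a small ambiguity, since the section speaks only of baseline and follow-up.

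In **Sample size**, state that the baseline-adjusted SD will be passed to the definitive trial alongside the raw SD.

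Optionally, plot each woman's change against her baseline score with control and intervention shown together, so that regression to the mean is not read as benefit. Keep this descriptive, with no subgroup SDs and no significance tests.

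The cost is a few lines of text and a little extra analysis of data already collected. Recruitment, visits and sample size are unaffected.

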## Discussion

The absence of mental health services in The Gambia, coupled with the stigma associated with mental illness in general, results in high levels of unmet need for pregnant women dealing with mental distress in The Gambia. The development of a low-cost, low-resource intervention, which is rooted in local health and cultural practices, is of high priority, and the feasibility study we intend to carry out will inform a full-scale trial to investigate efficacy of such an approach.

By employing local research assistants and creating a partnership with governmental agencies, such as The Ministry of Health & Social Welfare and The National Centre for Arts and Culture, this study brings the understanding of existing health services and access to a network of primary healthcare workers throughout the country as well as the diversity of local musical practices and the meanings attached to them. This valuable knowledge will help us cope with the practical and operational issues that may arise. We hope to disseminate our findings within various scientific publications, during field days in various areas in The Gambia, and during a meeting in London which will bring together the researchers as well community members, academic colleagues and health professionals interested in hearing about this work.

### Trial status

This article describes the protocol for a Community Health Intervention through Musical Engagement (CHIME) for perinatal mental health in The Gambia (version 1.0, 11/11/18). The sponsor for this trial is Goldsmiths, University of London. The project is funded by the MRC and the AHRC. Ethical approval was obtained from the Goldsmiths University Ethics Committee, the Research and Publication Committee (RePubliC) from the University of The Gambia and the Australian National University ethics committee.

## Data Availability

All of the data will be held by the principal investigator, and the research team has exclusive use of the data until the publication of the results.

## Abbreviations

AHRC: Arts and Humanities Research Council
CMHT: Community mental health team
EPDS: Edinburgh Postnatal Depression Scale
LMICs: Low- and middle-income countries
MRC: Medical Research Council
PACTR: Pan African Clinical Trial Registry
RAs: Research assistants
SRQ-20: Self-Reporting Questionnaire
